## Outcome Measures

| Type    | Name                                                   | Time Frame                                                                  | Brief Description                                                                                                                                                                                                                        |
|---------|--------------------------------------------------------|-----------------------------------------------------------------------------|------------------------------------------------------------------------------------------------------------------------------------------------------------------------------------------------------------------------------------------|
| Primary | Effective Collaboration (Quantitative)                 | Continuous                                                                  | The SIC will allow for continuous measurement of implementation success. Assessment of the SIC results will be ongoing with subsequent evaluation at the completion of the intervention period.                                          |
| Primary | Effective Collaboration (Qualitative and Mixed Method) | 42 months (6 months pre- and 6 month post-30-month LHS intervention period) | We will use a mixed method approach in evaluating the alliance, as measured by the effective collaboration survey as well as qualitative interviews, to assess for changes over time, between-system changes, and within-system changes. |
| Primary | Cascade                                                | 10 years, total                                                             | We will use administrative data to compare the effectiveness of                                                                                                                                                                          |

|         |                            |                                                                             |                                                                                                                                                                                                                                                                               |
|---------|----------------------------|-----------------------------------------------------------------------------|-------------------------------------------------------------------------------------------------------------------------------------------------------------------------------------------------------------------------------------------------------------------------------|
|         |                            | admin sample;
42 months LHS
intervention
sample                    | the LHS intervention on the Cascade (i.e., substance use treatment need identification, referral to services, initiation of services, and engagement in services).                                                                                                            |
| Primary | Criminal
recidivism     | 10 years, total
admin sample;
42 months LHS
intervention
sample | We will evaluate criminal recidivism across the 10-year administrative data collection period. We will assess if Cascade improvement is associated with decreased criminal recidivism. We will also assess if there are intervention-specific effects on criminal recidivism. |
| Primary | Opioid-related
outcomes | 10 years, total
admin sample;
42 months LHS
intervention
sample | We will use administrative data to assess opioid-related outcomes. We will assess if Cascade improvement is associated with decreased opioid-related outcomes. We will also assess if there are intervention-specific effects on opioid-related outcomes.                     |

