## Statistical Design and Power

### *Aim 3 Implementation Outcomes Analyses*

The analyses will proceed in two steps.

*Step 1.* We will use standard step wedge analytic methods (see citations in reference list for PASS report below). We will use linear mixed models to analyze repeatedly measured implementation variables to determine whether implementation variables change over time from the control to intervention conditions. Organizational survey data will be collected at the county level (from 164 JJ staff) and from the health system level (from 231 CMHC staff) for a total of 395 surveys collected at six time points at 6-month intervals: Study Months 8, 14, 20, 26, 32, 38. The following continuous scale scores will be analyzed in a separate model as the dependent variable: perceived readiness to implement new innovations (ORIC), climate support of adopting new innovations (ICS), organization's leadership support of implementation of evidence-based practice (ILS), and collaboration alliance between JJ/CMHC (Effective Collaboration subscale). The models will contain random effects to account for the clustering of survey participants within county and health system organizational levels. The models will contain the following independent variables: Time (Month 8, 14, 20, 26, 32, 38), and survey covariates (JPO age, sex, and race/ethnicity, time in current position, highest/type degree, number of previous positions, salary, caseload size, job (dis)satisfaction rating, turnover intentions, and burnout rating). The Time effect will be tested to determine whether implementation outcomes change over time. The Covariate-by-Time interaction will be tested to determine whether the implementation outcomes changed differently over time for particular covariate values. Alternative time covariance structures (e.g., autoregressive) will be considered. Alternative models will be compared with Akaike Information Criterion (AIC), with lowest AIC indicating the better model statistically.

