*Step 2.* The analyses will be similar to that described above in Step 1 except the implementation variables (readiness, climate support, leadership support, and collaborative alliance) will be used as independent variables to predict the dependent variable of implementation fidelity. Fidelity will be measured (in three separate models) using the SIC Pre-implementation score, the SIC Implementation score, and the SIC Sustainability score. In exploratory analyses, two additional fidelity dependent variables will be analyzed: percentage of activities performed, and Duration (number of days between activities). The analysis for Aim 4 describes how implementation climate and fidelity measures will be used in models as predictors of the SU cascade of care and opioid related outcomes.

*Aim 3 Power.* We require a total sample size of 384 enrolled (we will be conservative and enroll 395) JJ and CMHC staff for the implementation surveys. The actual analysis will employ linear mixed models that incorporate all staff participants with available implementation outcomes variables collected at multiple survey time points (Study Month 8, 14, 20, 26, 32, 38). The analysis models will actually also account for a second clustering variable (i.e., within each county, we will have surveys from staff of one

JJ system, and surveys from staff of one CMHC system), yielding 16 total clusters (8 counties by two JJ/CMHC sites within each county). However, the sample size inflation factor is greater with fewer clusters; therefore, for power calculations, we conservatively assumed 8 clusters instead of 16 total clusters. We used the PASS software to calculate power for a test comparing two means (control condition mean vs treatment condition mean) in a cluster-randomized step wedge design. Our step wedge design is an “incomplete design” in which a different number of clusters (i.e., counties) start the intervention at each step. Additional detail about the step wedge design, including clusters, cohorts, steps, timeline and design matrix, is provided below under the power section for Aim 4. Unlike Aim 4 which will have extensive (conservatively 6 months, actually 5 years) prior baseline administrative data for the control condition, the implementation scale data for Aim 3 is collected at a single baseline point (study month 8) and this will be used as the control condition measurement.

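### The Aim 3 survey model has no JJ-versus-CMHC term, so it cannot estimate the between-system and within-system changes declared for the Primary collaboration outcome

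*Protocol*

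**What the plan says.** The Outcome Measures table in section 7 makes Effective Collaboration (Qualitative and Mixed Method) a Primary outcome. The survey and the qualitative interviews together are "to assess for changes over time, between-system changes, and within-system changes".

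Step 1 of the Aim 3 Implementation Outcomes Analyses names the Effective Collaboration subscale as one of four dependent variables, each with its own linear mixed model. The fixed part is written out: "The models will contain the following independent variables: Time (Month 8, 14, 20, 26, 32, 38), and survey covariates". The covariate list runs through age, sex, race/ethnicity, time in position, degree, previous positions and salary, and ends with "caseload size, job (dis)satisfaction rating, turnover intentions, and burnout rating". Membership of JJ or CMHC is not on it.

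Two tests are declared. One is a test of Time alone, for any change across the six waves. The other asks whether that change depends on a covariate: "The Covariate-by-Time interaction will be tested to determine whether the implementation outcomes changed differently over time for particular covariate values".

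System appears only in the random part, which holds "random effects to account for the clustering of survey participants within county and health system organizational levels". The Aim 3 Power text describes this as 16 clusters, one JJ and one CMHC site in each of 8 counties. Surveys come from 164 JJ staff and 231 CMHC staff, 395 in all, at six time points.

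**The concern.** A random effect for organisation accounts for correlation among staff of the same agency. It does not produce a JJ-versus-CMHC contrast. A constant difference between the systems goes into the county-by-system variance. A different course over time in the two systems goes into the residual. System is not a listed covariate, so the Covariate-by-Time tests do not reach it either.

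The survey model therefore returns one Time effect averaged over both systems. Of the three comparisons named for this Primary outcome, it estimates only change over time.

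This matters because the study aims to build an alliance between two organisations. A gain felt by only one of them is a different finding from a gain felt by both, and the pooled Time effect looks the same in either case.

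**Working it through.** **1. The plan's own power figures.** Inputs: K = 8 counties, T = 6 periods, m = 8 respondents per county per period, SD 1.00, ICC 0.01, two-sided alpha 0.05 (Aim 3 Power and its PASS report), with the 3/3/2 design matrix from Aim 4 Power. The cross-sectional stepped-wedge variance of Hussey and Hughes is

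Var = K s² (s² + T τ²) / [(K U − W) s² + (U² + K T U − T W − K V) τ²],

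with τ² = 0.01 and s² = 0.99/m. From the matrix, U = 33, W = 237 and V = 141. So K U − W = 264 − 237 = 27, and the second bracket is 1089 + 1584 − 1422 − 1128 = 123.

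For m = 8: s² = 0.12375 and Var = 0.99 × 0.18375 / (3.34125 + 1.23) = 0.0398, so SE = 0.199. Power = Φ(d/SE − 1.96) gives 0.80, 0.85, 0.94 and 0.98 for d = 0.56, 0.60, 0.70 and 0.80. These match the protocol. The figures are correct, but they concern the pooled intervention-versus-control difference only.

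**2. What pooling does to a one-sided change.** The approximate weights are 164/395 = 0.415 (JJ) and 231/395 = 0.585 (CMHC).

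- JJ +0.5 SD, CMHC 0: pooled 0.5 × 0.415 = 0.21 SD.
- CMHC +0.5 SD, JJ 0: pooled 0.5 × 0.585 = 0.29 SD.
- CMHC +0.8 SD, JJ 0: pooled 0.8 × 0.585 = 0.47 SD.

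The last case was also simulated: 40 runs, 20 JJ and 29 CMHC staff per county per wave, assumed random-intercept SD 0.1, repeats independent. The stated model gave a mean last-wave Time effect of 0.46 SD, significant in all 40 runs. With System and System-by-Time added, the same data gave −0.02 SD for JJ and 0.81 SD for the CMHC-minus-JJ difference.

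**3. How well the difference can be estimated.** The formula in step 1 is applied to each system. The two estimates are treated as independent, so SE(difference) = √(SE²_JJ + SE²_CMHC). The detectable difference at 80% power is (1.96 + 0.8416) × SE = 2.8016 × SE. The protocol leaves two readings of the respondent count.

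| Reading | m, JJ | m, CMHC | SE, JJ | SE, CMHC | SE, difference | Detectable difference |
|---|---|---|---|---|---|---|
| All 395 at every wave, repeats independent | 164/8 = 20.5 | 231/8 = 28.9 | 0.128 | 0.110 | 0.169 | 0.47 SD |
| Each respondent counted once over six periods | 164/48 = 3.4 | 231/48 = 4.8 | 0.299 | 0.254 | 0.392 | 1.10 SD |

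The second row follows the PASS sizing, where N is the total over all clusters and periods. On that row, power for a difference of 0.5 SD is Φ(0.5/0.392 − 1.96), about 25%, and for 0.56 SD about 30%. On the first row, power for 0.56 SD is about 91%, and the detectable difference barely moves with the ICC (0.48 SD at 0.05 and at 0.10). The first row is optimistic because it assumes full response and treats six surveys of the same person as independent.

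These SEs are for the intervention effect, the contrast used in Aim 3 Power. A plain Time contrast would have a different precision.

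**The case against.** The outcome is mixed-method. The Outcome Measures row relies on interviews as well as the survey, and Assessing Outcomes plans three sets of qualitative and focus group interviews to be triangulated with the other data. Nothing in the table says that each comparison must be a fixed-effect contrast. This stands in part: the interviews can show qualitatively that one side changed and the other did not. But the table assigns the comparisons to the survey too, and the survey model is the only quantitative analysis given for it.

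System is also not ignored. It is a random level in Aim 3, and Aim 4 uses county-by-system survey scores, including collaborative alliance, as time-varying predictors. System-specific scores will therefore exist. Using them to predict cascade outcomes is still not an estimate of whether JJ and CMHC alliance changed differently. The comparison of alternative models by AIC does not fill the gap either: it follows the sentence on time covariance structures and commits to no system term.

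A statistical analysis plan could add the term. However, the protocol does not leave the model open. It itemises the terms and tests, and they do not match its own outcome definition.

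Two stronger readings are tempting. A reader might infer that a one-sided gain will be reported as a joint one. The protocol does not say so, the interviews may reveal the difference, and a small one-sided gain could instead be diluted to non-significance. A reader might also infer that the survey can comfortably separate the systems. That holds only on the optimistic reading of the respondent count. On the protocol's own sizing, it does not.

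**Conclusion.** The mismatch is real and rests on the protocol's text. The survey model given for the Effective Collaboration subscale estimates one of the three comparisons declared for this Primary outcome. It gives a pooled change, about 58% CMHC by staff numbers, that cannot distinguish a one-sided change from a joint one. The weights assume response in proportion to the 164 and 231 staff listed.

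The point is limited to the survey model. It does not show that the outcome as a whole cannot address system differences, or that the stated power is wrong.

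The detectable between-system difference in LHS effect lies between about 0.47 SD and 1.10 SD at ICC 0.01, depending on how many staff answer at each wave and how far repeats carry independent information. The difference should therefore be reported as an estimate with its interval, and a non-significant result should not be read as evidence that the systems changed alike.

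**What to change.** In Aim 3 Step 1, for the Effective Collaboration model:

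- Add System (JJ versus CMHC) and System-by-Time as fixed effects.
- Add System-by-LHS only if an explicit LHS indicator is also included. The listed variables contain none at present.
- Keep the county and county-by-system random effects.
- Report the change in each system and the difference between them, with confidence intervals.

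The alternative is to narrow the Outcome Measures row so that the survey is said to assess change over time only, leaving system comparisons to the interviews.

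No new data are needed. The cost is two model terms (three with System-by-LHS) and a sentence on reporting. System-by-Time with six categorical waves uses 5 degrees of freedom. System-specific estimates, and especially the difference, will be less precise than the pooled change: on the every-wave reading the SE for the LHS effect is 0.085 pooled (m = 395/8 = 49.4), against 0.128 (JJ), 0.110 (CMHC) and 0.169 (difference).

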## Statistical Design and Power

### *Aim 3 Implementation Outcomes Analyses*

The analyses will proceed in two steps.

*Step 1.* We will use standard step wedge analytic methods (see citations in reference list for PASS report below). We will use linear mixed models to analyze repeatedly measured implementation variables to determine whether implementation variables change over time from the control to intervention conditions. Organizational survey data will be collected at the county level (from 164 JJ staff) and from the health system level (from 231 CMHC staff) for a total of 395 surveys collected at six time points at 6-month intervals: Study Months 8, 14, 20, 26, 32, 38. The following continuous scale scores will be analyzed in a separate model as the dependent variable: perceived readiness to implement new innovations (ORIC), climate support of adopting new innovations (ICS), organization's leadership support of implementation of evidence-based practice (ILS), and collaboration alliance between JJ/CMHC (Effective Collaboration subscale). The models will contain random effects to account for the clustering of survey participants within county and health system organizational levels. The models will contain the following independent variables: Time (Month 8, 14, 20, 26, 32, 38), and survey covariates (JPO age, sex, and race/ethnicity, time in current position, highest/type degree, number of previous positions, salary, caseload size, job (dis)satisfaction rating, turnover intentions, and burnout rating). The Time effect will be tested to determine whether implementation outcomes change over time. The Covariate-by-Time interaction will be tested to determine whether the implementation outcomes changed differently over time for particular covariate values. Alternative time covariance structures (e.g., autoregressive) will be considered. Alternative models will be compared with Akaike Information Criterion (AIC), with lowest AIC indicating the better model statistically.

*Step 2.* The analyses will be similar to that described above in Step 1 except the implementation variables (readiness, climate support, leadership support, and collaborative alliance) will be used as independent variables to predict the dependent variable of implementation fidelity. Fidelity will be measured (in three separate models) using the SIC Pre-implementation score, the SIC Implementation score, and the SIC Sustainability score. In exploratory analyses, two additional fidelity dependent variables will be analyzed: percentage of activities performed, and Duration (number of days between activities). The analysis for Aim 4 describes how implementation climate and fidelity measures will be used in models as predictors of the SU cascade of care and opioid related outcomes.

*Aim 3 Power.* We require a total sample size of 384 enrolled (we will be conservative and enroll 395) JJ and CMHC staff for the implementation surveys. The actual analysis will employ linear mixed models that incorporate all staff participants with available implementation outcomes variables collected at multiple survey time points (Study Month 8, 14, 20, 26, 32, 38). The analysis models will actually also account for a second clustering variable (i.e., within each county, we will have surveys from staff of one

JJ system, and surveys from staff of one CMHC system), yielding 16 total clusters (8 counties by two JJ/CMHC sites within each county). However, the sample size inflation factor is greater with fewer clusters; therefore, for power calculations, we conservatively assumed 8 clusters instead of 16 total clusters. We used the PASS software to calculate power for a test comparing two means (control condition mean vs treatment condition mean) in a cluster-randomized step wedge design. Our step wedge design is an “incomplete design” in which a different number of clusters (i.e., counties) start the intervention at each step. Additional detail about the step wedge design, including clusters, cohorts, steps, timeline and design matrix, is provided below under the power section for Aim 4. Unlike Aim 4 which will have extensive (conservatively 6 months, actually 5 years) prior baseline administrative data for the control condition, the implementation scale data for Aim 3 is collected at a single baseline point (study month 8) and this will be used as the control condition measurement.

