The amount of time (in days) exposed to the implementation for each adolescent arrestee will be accounted for in the rate ratio by defining the "offset" variable as the natural log of the number of days of exposure for every 6-month period of implementation. The primary denominator will be the number of arrested youth in the rolling intake cohort (e.g., % referred as a percentage of the number in the arrestee intake cohort). For some outcomes, another separate outcome will be derived and analyzed using a smaller denominator (e.g., % referred as a percentage of YJJ in need of treatment). The denominator for % in need (i.e., % screened positive) will be YJJ screened. The denominator for the % engaged will be the YJJ initiated. Because some youth will have multiple arrests, they could also have multiple screenings. In addition, for a single arrest and single screening, there could be multiple referral events over any 6-month period; for a single referral, there could be multiple treatment initiation events; and for a single treatment initiation, there could be multiple occurrences of an engaged event (i.e., 2+ behavioral health visits within 30 days after initiation) over any 6-month period. Therefore, the model will capture these multiple events as counts for every 6-month period.

Covariate-by-6-Month-Period interactions will be tested to determine whether the outcome response rates changed differently over time for different values of covariates.

In addition, youth-level covariates (demographics and health visit data) will also be included as predictors.

In the next step of the model, we will include organizational-level (i.e., county-by-system [JJ and CMHC]) survey predictors including staff characteristics (JPO age, sex, and race/ethnicity, time in current position, highest/type degree, number of previous positions, salary, caseload size, job (dis)satisfaction rating, turnover intentions, and burnout rating), implementation variables (readiness,

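### Aim 3 Step 2 puts an organisation-level SIC score into a staff-level model with no term for the value that staff in a unit share at each wave

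*Protocol*

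**What the plan says.** Protocol, Aim 3 Implementation Outcomes Analyses. Step 1 fits linear mixed models to staff survey scales, with 164 JJ and 231 CMHC staff, "for a total of 395 surveys collected at six time points at 6-month intervals". On clustering it says: "The models will contain random effects to account for the clustering of survey participants within county and health system organizational levels".

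Step 2 opens by taking over that analysis: "The analyses will be similar to that described above in Step 1 except the implementation variables" change their role. Those variables are the survey scales for readiness, climate, leadership and alliance. Outcomes in Step 1, they now "will be used as independent variables to predict the dependent variable of implementation fidelity". The outcome is defined as follows: "Fidelity will be measured (in three separate models) using the SIC Pre-implementation score, the SIC Implementation score, and the SIC Sustainability score". Percentage of activities performed and duration are added with the words "In exploratory analyses, two additional fidelity dependent variables will be analyzed". Step 2 does not mention averaging the surveys.

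The Aim 3 Power paragraph describes the rows of the Aim 3 models: "The actual analysis will employ linear mixed models that incorporate all staff participants with available implementation outcomes variables collected at multiple survey time points".

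Two other places fix the nature of the SIC. Assessing Outcomes describes it as an eight-stage, observation-based tool that measures completion of implementation activities. Aim 4 Analyses says "In the next step of the model, we will include organizational-level (i.e., county-by-system [JJ and CMHC]) survey predictors", puts the three SIC scores in that list, and treats the implementation and fidelity measures as time-varying.

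**The concern.** Step 1 has a staff-level outcome, so staff rows with cluster effects are natural. Step 2 replaces that outcome with a score that describes the implementing organisation. Two colleagues in the same unit cannot differ on it at the same wave. Adding staff rows then adds no information on the outcome, yet the model counts each row as a further observation.

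At stake is the trial's statement on which of readiness, climate, leadership and alliance go with better fidelity. If the standard errors are set by the number of staff and not by the number of organisations and waves, chance associations will be reported as findings.

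**Working it through.** **1. The plan's own figure.** The only Aim 3 power figures concern the Step 1 comparison of control and intervention means. The inputs are 8 clusters, 6 periods, 8 staff per cluster per period, N = 384, ICC 0.01, SD 1, two-sided alpha 0.05, and the 3/3/2 design matrix given under Aim 4 Power. The Hussey-Hughes variance with a Wald Z-test gives 0.802, 0.853, 0.939 and 0.980 for differences of 0.56, 0.60, 0.70 and 0.80. The protocol states 0.80, 0.85, 0.94 and 0.98, so these reproduce. There is no figure for Step 2.

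**2. How many staff share a value.** The protocol allows three readings:
- SIC scored per county, 395 staff at each wave: 395/8 = 49.4 staff per unit.
- SIC scored per county-by-system: 395/16 = 24.7 staff per unit.
- Staff numbers as in the Aim 3 PASS report: 8 per county per wave (8 × 6 × 8 = 384).

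**3. If the SIC varies by wave.** A unit random effect removes what is constant in the unit over time. The part of the SIC specific to a unit at one wave stays in the residual and is identical for all m staff in that cell. Let s be the share of predictor variance common to staff in the same unit and wave. For a slope whose outcome is constant within the cell,

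DEFF = 1 + (m − 1) × s, and actual type I error = 2 × [1 − Φ(1.96/√DEFF)].

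Example with m = 49.4 and s = 0.05: DEFF = 1 + 48.4 × 0.05 = 3.42, 1.96/√3.42 = 1.06, type I error 0.29.

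| Reading | s = 1% | s = 5% | s = 10% |
|---|---|---|---|
| 8 units, 49 staff: DEFF | 1.48 | 3.42 | 5.84 |
| formula / simulation | 11% / 11% | 29% / 29% | 42% / 45% |
| 16 units, 25 staff: DEFF | 1.24 | 2.18 | 3.37 |
| formula / simulation | 8% / 9% | 19% / 21% | 29% / 30% |
| 8 units, 8 staff: DEFF | 1.07 | 1.35 | 1.70 |
| formula / simulation | 6% / 5% | 9% / 10% | 13% / 16% |

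The simulations had no true association, six waves, unit and wave effects in the model, and a further 1% of predictor variance at unit level. The same data averaged to one row per unit-wave rejected 4% to 6% of the time.

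Fitted mixed models with a county random intercept (150 runs per setting, s equal at county and county-wave level) agree. With 49 staff per cell they rejected about 9%, 34% and 41% at s = 1%, 5% and 10%. With 8 per cell they rejected 5% and 11% at 1% and 5%.

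**4. If the SIC is constant within the unit.** The unit random intercept then reproduces the outcome exactly. A test fit gave a residual variance of about 1e-12, with the slope and its standard error both about 0. This is a failed model, not an optimistic one.

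**5. The information really available.** With one value per unit, a single correlation needs |r| above 0.707 (8 units) or 0.497 (16 units) to reach 5%; 395 rows treated as independent would need only 0.099. Four predictors together leave 8 − 5 = 3 or 16 − 5 = 11 residual degrees of freedom. With six waves, unit and wave effects, and four predictors, unit-wave rows leave at most 7 × 5 − 4 = 31 or 15 × 5 − 4 = 71.

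**The case against.** The strongest reply has four parts.

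- Step 2 is only said to be similar to Step 1. The sentence on staff participants stands in the power paragraph, and Aim 4 uses the same surveys at organisational level, so averaging could be left to the SAP. In part this stands: a SAP could repair it. But the protocol does fix the model family, outcome and predictors, and it describes the random effects as handling survey participants. Taken as written, the rows are staff.
- A reader might infer that one county score is repeated across about 49 staff. The documents do not establish this. Nowhere is the SIC said to be scored once per county, and Aim 4 points to county-by-system units and time-varying values. This stands, which is why three readings are carried above.
- A reader might infer that the tests are far too optimistic. The only ICC in the protocol is 0.01, a Step 1 planning input. At that level of sharing the error is about 5% to 12%, and with 8 staff per cell there is hardly any inflation. This stands too. The larger figures need more sharing. That is plausible for scales that ask staff about their own organisation, but it is assumed here.
- A reader might infer from the exploratory label on two extra outcomes that the three SIC models are confirmatory. The protocol does not say so. The survey-to-SIC association is not among the listed outcome measures, although the SIC itself underlies one of the primary outcomes.

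**Conclusion.** The point holds in a conditional form. Step 2 sets an outcome that varies only by organisation and wave against staff-level rows, and the stated random effects do not cover the shared unit-by-wave value. If the SIC varies by wave, a nominal 5% test rejects about 11% to 45% (8 units of 49 staff), 9% to 30% (16 units of 25) or 5% to 16% (8 units of 8 per wave). If the SIC is constant within the unit, the model cannot be estimated usefully.

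The ranges rest on assumed predictor sharing of 1% to 10% within unit-wave and on three readings of the staff numbers. The mismatch of level rests on none of these assumptions; only its size does.

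A reader might extend the point to the organisational predictors added in the Aim 4 next step. The documents do not support that here: they do not say that all predictors enter one model together, the model and outcomes differ, and no calculation was made.

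**What to change.** State in Step 2 the unit at which the SIC is scored (county or county-by-system) and whether each phase score changes from wave to wave. Then:

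- Average each survey scale to that unit and wave, and fit one row per unit-wave with a unit effect, a wave effect and small-sample degrees of freedom (for example Kenward-Roger).
- Where a phase score is a single value per unit, report its association with the survey means descriptively.
- Label all of Step 2 exploratory, not only the two additional fidelity variables.

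The cost is a change of wording and no new data. Intervals will be wider and degrees of freedom fewer, which reflects the 8 or 16 organisational units that the trial has.
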